#### In- and exclusion criteria for patients

To be eligible, patients have to be (i) clients of a participating home care service, (ii) aged 60 years or older, (iii) assigned to a care grade of 1 or higher, and (iv) rated into a life-expectancy of at least 4 weeks. Furthermore, (v) adequate German language skills, and (vi) the cognitive ability to follow the intervention and data collection are required. The latter will be assessed using the stepwise approach of the Dementia Screening Scale (DSS), a validated seven-item proxy instrument for nurses where a score of “0” indicates no cognitive impairment and “14” the most severe cognitive impairment [26]. Patients with a total DSS score < 3 will be included in the study whereas those scoring between 3 and 5 will only be eligible if the respective key nurses consider them competent to follow the intervention and to give informed consent. No further exclusion criteria will be applied.

An expected mean of 30 patients are aimed to be included per home care service (*n* = 960 patients).

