### Sample size

To detect an effect size of 0.35 (Cohens d), which corresponds to a medium effect, with respect to the primary endpoint after 12 months between the intervention and the control group with 90% power (β = 0.10) using a two-sided significance level of 5% (α = 0.05) based on the t-test, a non-cluster study setting would require a total of 173 patients per group. Taking cluster sampling into account [52], we used an intra-cluster correlation coefficient (ICC) of 0.05 in accordance with a study on the effectiveness of ACP in the Netherlands of Korfage et al. [20]. Assuming an average cluster size of 30 participants per home care service, the design factor is 2.45 and 15 clusters are required per group. Estimating that two home care services might drop out [21], 32 clusters with a total of 960 participants will be included in the study.

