### Data analysis

Data analyses will be conducted by a blinded biometrician (BH), who does not know, which group is intervention or control, following Good Clinical Practice (GCP) standards. All analyses will be cluster-adjusted and follow the intention-to-treat principle.

Baseline characteristics will be displayed descriptively. The primary outcome (PAM-13-D) will be compared between intervention and control group using a mixed model (α = 0.05, two-sided) and adjusted for fixed (baseline values including initial value of PAM-13-D) and random (cluster) effects. For patients who early terminated the study, last observations (information at the last point of measurement) will be carried forward (LOCF imputation). For sensitivity, the same analysis will be performed as complete case analysis without LOCF. Furthermore, a more detailed analysis comparing the longitudinal course of the primary outcome in the interim time points after 6 and 12 months without imputation will be investigated using a mixed model with the intervention and initial PAM-13-D values as fixed effects, clusters as a random effect, and using covariance patterns to adjust for repeated measurement.

Mixed models will also be used for all secondary endpoints, taking into account cluster effects or repeated measurements. Survival analyses will be conducted using stratified Kaplan-Meier curves and Cox regression. Subgroup analyses will be conducted stratified by age and sex.

Economic analyses on patient level will include individual total costs over 12 months. Differences between intervention and control group will be estimated using Gamma regression, again accounting for cluster effects. Adjustment is planned for prematurely dropped out. On organizational level (implementation and intervention costs from the perspective of home care services) descriptive analyses are will be performed.

For the process evaluation, qualitative data (interviews and focus groups) will be summarised and narratively described [53] supported by MAXQDA. Further, quantitative data (questionnaires with closed- and open-ended questions) will be analysed using descriptive statistics.

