### Data management

All data will be collected by blinded study assistants at each study site using standardised Case Report Forms (CRFs). Afterwards, the CRFs will be digitalised using the data management system secuTrial®. Extensive plausibility checks and data validation will be conducted by the trained researcher (BW), who has also developed and proven the database following GCP rules. Data of drop outs will be analysed until drop out date (intention-to-treat), except the withdrawing consent goes along with the wish to delete all data. All personalised contact data and key lists remain under lock at the respective study site so that confidentiality will be preserved.

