### Limitations

As the ACP intervention will be provided only in German and only to patients being cognitively able to follow the intervention, patients with inadequate German language skills or with dementia will be excluded. As the study participation will take at least 40 h per home care service at the intervention group as well as the target population is a vulnerable older group, it cannot be excluded, that higher drop-out rates will occur. Drop-outs might cause a potential bias. We plan analyses using imputation by LOCF without multiple imputation, and additionally an analysis of the complete time course to discuss a possible bias of the result form drop-outs.

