### Strengths

The study has several strengths. We will assess the effectiveness of ACP for the first time in the home care setting. Further, the cluster-randomised design will provide a high level of evidence on the question whether patient activation may be increased by our intervention. Apart from the experimental interventions, control and intervention group clusters will be treated equally in order to prevent performance bias. As successfully performed in previous studies [29, 61, 62], we will spend a lot of effort to avoid cluster drop-outs (e.g. by regularly telephone calls with the BEVAs and various offers for support), which could lead to cluster imbalance and pronounced lost to follow up. Additionally, the study duration of 12 months provides the possibility to assess long-term effects.

A further strength of our study is the extensive process evaluation since changing attitudes or behaviours in complex interventions pose the challenge of determining how contextual components of participants and home care services interact and influence the intended outcome.

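### LOCF as the primary handling of missing 12-month PAM-13-D biases the treatment effect, in a direction that cannot be known in advance, although a better analysis is already planned

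*Protocol article*

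**What the plan says.** The primary outcome is PAM-13-D at 12 months. PAM is measured at baseline (t0), 6 months (t1) and 12 months (t2), so a carried value comes from t0 or t1. Under Data analysis, the primary comparison is a mixed model with baseline values, including baseline PAM-13-D, as fixed effects and cluster as a random effect. For missing values the rule is: "For patients who early terminated the study, last observations (information at the last point of measurement) will be carried forward (LOCF imputation". The Limitations section confirms it: "We plan analyses using imputation by LOCF without multiple imputation".

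Two further analyses are named: a complete-case version as sensitivity analysis, and a longitudinal mixed model of the 6- and 12-month values without imputation. The fixed effects named for the latter are intervention and initial PAM-13-D.

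On loss, patients need only be "rated into a life-expectancy of at least 4 weeks", against 12 months of follow-up. Limitations concedes that drop-out may be high and could cause bias, and links this partly to the workload of at least 40 hours per intervention service. Sample size provides for two lost services and states no allowance for individual patients. Death is listed as a reason for discontinuing the intervention, and mortality is a separate secondary outcome. The LOCF rule mentions no exception for deaths.

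**The concern.** A carried value answers a different question from the one asked at 12 months. If it is the baseline value, the patient's change is zero by construction in either arm. If it is the t1 value, the patient contributes the 6-month effect. The primary estimate is therefore a mixture of zero, the 6-month effect and the 12-month effect, weighted by when patients leave. If leaving differs by arm and scores drift over time, part of that drift is counted as a treatment effect.

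The size and sign of the error thus depend on the drop-out pattern, which cannot be known beforehand, so LOCF cannot be defended as conservative. At stake is the headline estimate of the trial and its confirmatory test. As the rule is worded, a patient who died could also be given a 12-month activation score.

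**Working it through.** **The plan's own figures.** Inputs from Sample size: "To detect an effect size of 0.35 (Cohens d"), 90% power, "using a two-sided significance level of 5"%, ICC 0.05, 30 patients per cluster.

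- The normal approximation, 2 × (1.960 + 1.282)² / 0.35², gives 172 per group. The exact t-test version gives 173, as stated: "a non-cluster study setting would require a total of 173 patients per group".
- Design factor: 1 + 29 × 0.05 = 2.45.
- Clusters: 173 × 2.45 = 423.85; 423.85 / 30 = 14.1, rounded up to 15 per group.
- Total: 2 × 15 + 2 = 32 clusters; 32 × 30 = 960.

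All stated figures reproduce.

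**What LOCF estimates.** For arm I (intervention) or C (control), let p2 be the share lost between t1 and t2, and q the share observed at t2; the remainder is lost before t1. Let e6 and e12 be the true effects, and m6 and m12 the control-arm changes from baseline, all in SD. If loss is unrelated to outcome and baseline means are equal, the expected LOCF difference is

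p2(I)·e6 + q(I)·e12 + [p2(I) − p2(C)]·m6 + [q(I) − q(C)]·m12.

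Patients lost before t1 add nothing to the effect terms.

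**Assumptions not in the article:** the loss rates, effect courses and trends below, loss unrelated to outcome, and a visit correlation of 0.6. The simulation used 16 + 16 clusters of 30, ICC 0.05, a baseline-adjusted cluster-level comparison and 3,000 runs per scenario.

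| Scenario | Formula | Simulated LOCF | 95% CI coverage |
|---|---|---|---|
| A. Effect 0.35 at both visits; 15% lost before and 15% after t1 | 0.15×0.35 + 0.70×0.35 = 0.298 | 0.296 | 0.90 |
| B. Effect grows 0.15 to 0.35; same loss | 0.15×0.15 + 0.70×0.35 = 0.268 | 0.269 | 0.81 |
| C. Effect wanes 0.45 to 0.25; same loss | 0.15×0.45 + 0.70×0.25 = 0.243 | 0.241 | 0.94 |
| C2. Effect wanes 0.55 to 0.25; 5% before, 25% after t1 | 0.25×0.55 + 0.70×0.25 = 0.313 | 0.310 | 0.89 |
| D. No effect; scores fall 0.15 then 0.30; loss 40% v 20%, half before t1 | 0.10×(−0.15) − 0.20×(−0.30) = 0.045 | 0.044 | 0.92 (type I error 0.082) |
| E. Effect 0.35; scores fall 0.20 then 0.50; loss as D | 0.80×0.35 − 0.02 + 0.10 = 0.36 | 0.360 | 0.96 |
| E2. Effect 0.15; scores fall 0.25 then 0.50; loss as D | 0.80×0.15 − 0.025 + 0.10 = 0.195 | 0.193 | 0.91 |

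In D, E and E2 the larger loss is in the intervention arm. Complete-case estimates were within 0.002 of the truth throughout, with coverage of about 0.95. That is expected, because loss was made unrelated to outcome; LOCF fails even in this benign setting.

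If all loss occurs before t1, a 12-month effect of 0.35 shrinks to 0.35 × (1 − p): 0.315, 0.28 and 0.245 at 10%, 20% and 30% loss. A separate simulation at 30% equal loss gave 0.24 to 0.30 with coverage of 75% to 91%, and a type I error of about 0.07 under unequal loss with falling scores.

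**Where the under-coverage comes from.** In scenario A the mean LOCF standard error was 0.0749 and the actual spread of the estimates 0.0761, so the two agree. The bias is 0.350 − 0.296 = 0.054, or 0.054 / 0.0761 = 0.71 sampling SDs. With the t quantile 2.04 (30 df): 2.04 × 0.0749 / 0.0761 = 2.01, and Φ(2.01 − 0.71) − Φ(−2.01 − 0.71) = 0.903 − 0.003 = 0.90, the simulated coverage. Bias alone explains it.

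**The case against.** The strongest defence is that the plan already includes a complete-case analysis and a longitudinal model without imputation, and openly discloses possible drop-out bias and the absence of multiple imputation. That is true and softens the point, but if the analyses disagree the LOCF result remains the confirmatory one. It is also fair that no drop-out rate is given and that under some patterns (C and E) the errors nearly cancel. The plan cannot count on that.

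Several stronger readings are tempting but not supported:

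- **LOCF always pulls the effect towards zero.** C2, D and E2 show the opposite.
- **LOCF costs power.** Diluting the effect while holding the standard error fixed suggests so, but the standard error shrinks too. In scenario A the ratio of estimate to standard error is 0.296 / 0.075 = 3.9 for LOCF and 0.348 / 0.091 = 3.8 for complete case. Under a constant effect the separate simulation gave power of 0.86 to 0.88 against 0.86 to 0.87. No power loss relative to complete case is shown.
- **The intervals are falsely narrow.** The LOCF standard error matches the spread of the LOCF estimate. The intervals are centred in the wrong place.
- **Data management contradicts LOCF.** "Data of drop outs will be analysed until drop out date (intention-to-treat") can be read as keeping the data collected before drop-out, which are the data LOCF uses.
- **Retention effort differs by arm.** The calls ("by regularly telephone calls with the BEVAs and various offers for support") are one example given for avoiding cluster drop-out, next to a statement that both arms are otherwise treated equally. They are not evidence of unequal patient loss.
- **The plan states that values are imputed after death.** It does not. This is an inference from the lack of an exception, and a detailed rule may stand in an analysis plan not shown here.

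**Conclusion.** The concern holds as a matter of bias. With LOCF as the primary rule in a baseline-adjusted model, the 12-month estimate is diluted when loss is equal and the effect is stable or growing: from 0.35 to about 0.24 to 0.30 SD at 30% loss, with coverage of 75% to 91%. It can be inflated when the effect wanes (0.25 to 0.31 SD in C2) or when loss differs by arm while scores drift (a spurious 0.04 SD and a type I error of 0.07 to 0.08 in D). The mechanism follows from the stated text. The sizes rest on assumed loss, trends and correlations, and on loss unrelated to outcome. The article's own remarks on life expectancy, drop-out and intervention workload make material and possibly unequal loss plausible, but do not quantify it. The treatment of deaths is a gap in the wording of the rule, not a stated error.

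**What to change.** Before unblinding:

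1. Make the longitudinal mixed model of t1 and t2 without imputation the primary analysis. Fixed effects: arm, visit, arm-by-visit and baseline PAM-13-D; cluster as a random effect; a covariance pattern for repeated measures. Name the 12-month arm contrast as the primary test. The visit and arm-by-visit terms must be added, because the model as described does not name them and without the interaction does not isolate the 12-month effect.
2. Demote LOCF to a sensitivity analysis. Add a multiple-imputation or delta-adjusted analysis to show how far the result depends on what is assumed about the missing values.
3. State that no PAM value is carried forward past death, and report mortality by arm beside the estimate. Say in words to whom the estimate refers, because a model that uses t1 values of patients who later die is not purely an analysis of 12-month survivors.

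The cost is small: the t1 data are already scheduled and the model needs only the added terms. The downside is that patients with no follow-up PAM do not contribute and the interval is somewhat wider. As a guide, the complete-case standard error in scenario A was 0.091 against 0.075 under LOCF. The new primary model still relies on loss being explained by the observed data, which is why the check in step 2 is needed.

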### Data management

All data will be collected by blinded study assistants at each study site using standardised Case Report Forms (CRFs). Afterwards, the CRFs will be digitalised using the data management system secuTrial®. Extensive plausibility checks and data validation will be conducted by the trained researcher (BW), who has also developed and proven the database following GCP rules. Data of drop outs will be analysed until drop out date (intention-to-treat), except the withdrawing consent goes along with the wish to delete all data. All personalised contact data and key lists remain under lock at the respective study site so that confidentiality will be preserved.

### Trial status

Home care service recruitment started in April 2019 and patient recruitment was completed in January 2020. The baseline was also completed in January 2020 and the 12-month follow-up will accordingly be completed in January 2021. Analyses will be completed in March 2021.

### Patient and public involvement

Patients and public were not involved in the definition of the research questions or outcome measures. However, patients and their relatives were involved in the pilot study, as feasibility and acceptability were tested also from their point of view. Additionally, one of the largest organisations of relatives of care dependent persons in Germany supports the STADPLAN study and is represented on the advisory board representing medical, statistical, medical law, ethics and patient advocacy expertise. Furthermore, pilot study results were presented and discussed on international conferences before finalizing the concept for the main study.

## Discussion

The STADPLAN study takes place given the fact that most of the recent international publications on ACP interventions were conducted or are actually running in the primary care setting [54–56] or in the hospital setting [57–59] after a time of investigating ACP mainly in the nursing home setting [60]. However, more evidence on the effectiveness of ACP-interventions in different settings is needed, also taking into account the structures of respective healthcare systems. STADPLAN is the first study in Germany that assesses an adapted ACP intervention in the home care service setting using trained nurses as facilitators. Furthermore, it is the first study internationally that focuses on the effectiveness and costs of ACP in community-dwelling older persons. Results will help to improve understanding and communicating patients’ will regarding future medical treatment and care, and thereby contribute to patients´ autonomy at the end of life.

### Limitations

As the ACP intervention will be provided only in German and only to patients being cognitively able to follow the intervention, patients with inadequate German language skills or with dementia will be excluded. As the study participation will take at least 40 h per home care service at the intervention group as well as the target population is a vulnerable older group, it cannot be excluded, that higher drop-out rates will occur. Drop-outs might cause a potential bias. We plan analyses using imputation by LOCF without multiple imputation, and additionally an analysis of the complete time course to discuss a possible bias of the result form drop-outs.

### Strengths

The study has several strengths. We will assess the effectiveness of ACP for the first time in the home care setting. Further, the cluster-randomised design will provide a high level of evidence on the question whether patient activation may be increased by our intervention. Apart from the experimental interventions, control and intervention group clusters will be treated equally in order to prevent performance bias. As successfully performed in previous studies [29, 61, 62], we will spend a lot of effort to avoid cluster drop-outs (e.g. by regularly telephone calls with the BEVAs and various offers for support), which could lead to cluster imbalance and pronounced lost to follow up. Additionally, the study duration of 12 months provides the possibility to assess long-term effects.

A further strength of our study is the extensive process evaluation since changing attitudes or behaviours in complex interventions pose the challenge of determining how contextual components of participants and home care services interact and influence the intended outcome.

## Data Availability

Not applicable.

## Abbreviations

ACP: Advance Care Planning
AD: Advance directive
BEVAs: Trained nurse facilitator
CRF: Case report form
DSS: Dementia Screening Scale
GP: General practitioner
HADS: Hospital Anxiety and Depression Scale
ICC: Intra-cluster correlation coefficient
LOCF: Last observation carried forward
NH: Nursing home
PAM: Patient Activation Measure
RA: Research assistant
STADPLAN: Study on advanced care planning in care dependent community-dwelling older persons
